### Recruitment

NASCITA will be embedded in Italian pediatric primary care practice. The coordination center has collaborated over the years with a network of hundreds of family pediatricians, as documented by numerous collaborative publications [19–22], which represents the first interlocutor to whom we proposed participation in the study. The basis of this network is the national Pediatric Cultural Association (ACP), with around 2000 members consisting mainly of family pediatricians. In order to have as large a sample as possible we therefore used the already existing network to begin the first identification of the locally representative pediatricians, who were then asked to identify additional pediatricians, not necessarily belonging to the ACP, in their areas for participation. Other pediatric scientific societies and associations will be contacted to expand collaboration and the number of participating pediatricians. In this regard, detailed information concerning the study will be disseminated through national pediatric journals and internet-based resources to increase recruitment. Recruitment will be based on the voluntary participation of interested pediatricians who can guarantee seven years of professional activity so that they can follow the enrolled newborns for the whole study period. This approach to enrolling pediatricians can be defined as a mixed method using also non-probability sampling techniques (convenience and purposive sampling) applied to choose a sample of subjects/units from a population [23, 24]. In terms of the work effort requested of the pediatricians, case report forms were discussed with a group of family pediatricians and tested by them in a pilot phase. The time needed to fill the forms was recorded by each participant and difficulties or doubts were reported to the coordinating center. The participants in the pilot phase assured the coordinating team that the data collection was feasible.

Recruitment of the newborns (and their parents) will take place during the first routine well child visit scheduled for all newborns within their first 45 days of life at the office of the pediatrician assigned to them by the LHU to which they belong. Parents will receive oral and written information about the purpose and methods of the study and will be invited to participate. If they agree to participate, they will be asked to sign an informed consent. Recruitment of newborns will begin in April 2019, while recruitment of pediatricians will begin in the preceding months.

### Study population size

The NASCITA cohort is sized to have enough power to study relatively common child exposures and outcomes. Table 1 reports the national prevalence of certain health characteristics of Italian children and the expected number of cases for different enrolling scenarios in order to obtain a minimum number of participants that would permit all these characteristics to be sufficiently represented. The aim is to recruit no less than 5000, and hopefully at least 10,000, newborns with complete information collected over the period of the study. We hypothesize that, given the fact that the data collection is based on routine visits by the pediatrician, attrition in NASCITA will be irrelevant for at least the first two years. Considering the previous experience of other Italian cohorts, NINFEA [34] and PiccoliPiù [16], we estimate a 20% loss to follow-up after the first two years.

**Table 1 Tab1:** National prevalence of certain health characteristics of Italian children and the expected cases for different enrolling scenarios in the NASCITA cohort study

Characteristics	Italian prevalence (%)	5.000 enrollments (n°)	10.000 enrollments (n°)	15.000 enrollments (n°)
Sex (% male) [25]	51.3	2565	5130	7695
Gestational age at birth [25]				
• < 37 weeks	6.9	345	690	1035
• 37–40 weeks	92.3	4615	9230	1385
• > 40 weeks	0.9	45	90	135
Twins/multiple birth [25]	1.7	85	170	255
Live birth rate after medically assisted procreation [25]	2.14	107	214	321
Birth defects [26]	2.0	100	200	300
Language disorders Age 3.5 years [27]	7.5	375	750	1125
Maternal smoking during pregnancy [28]	7	350	700	1050
Breastfeeding (exclusive) [29]				
• Until age 6 months	42.7	2135	4270	6405
• 6–12 months	5.5	275	550	825
Parental history of atopy [30]	22–37	1100–1850	2200–3700	3300–5550
Eczema prevalence Age 36 months-5 years [30]	21.0	1050	2100	3150
Wheezing prevalence Age 36 months-5 years [31, 32]	25.2	1260	2520	3780
Overweight prevalence Age 2–6 years [33]	16	800	1600	2400

With an expected minimum of 5000 newborns, representing about 1% of the newborns in Italy, and with an estimated 20% loss to follow-up, the resulting sample size of 4000 children will still give NASCITA enough power to study common childhood exposures and outcomes [16].

With the parents’ consent, data on children withdrawing after 12 months of age will be considered in the analysis for the relevant time period of participation (e.g. rate of exclusive breastfeeding, reading out loud, SIDS prevention, etc.). Data will be deleted upon parents’ request.

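### The size target is stated in two incompatible ways (5000 complete, or 5000 enrolled leaving 4000), and Table 1 gives its later outcomes no allowance for the plan's own loss

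*Protocol article*

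**What the plan says.** All of this is in the protocol article, Methods, Study population size, unless noted.

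- **Target.** The aim is to "recruit no less than 5000, and hopefully at least 10,000, newborns with complete information collected over the period of the study".
- **Attrition.** The article expects that "attrition in NASCITA will be irrelevant for at least the first two years" and then, from the experience of two other Italian cohorts, "we estimate a 20% loss to follow-up after the first two years". It does not say how the loss is spread between ages 2 and 6.
- **Resulting size.** The closing sentence starts from 5000 as the intake ("With an expected minimum of 5000 newborns, representing about 1% of the newborns in Italy") and concludes that "the resulting sample size of 4000 children will still give NASCITA enough power to study common childhood exposures and outcomes".
- **Table 1.** It lists national prevalences and expected cases for 5000, 10,000 and 15,000 enrolments. The text presents it as the way to find a minimum number of participants at which every listed characteristic is adequately represented. Four rows concern later ages: language disorders (3.5 years), eczema and wheezing (both 36 months to 5 years) and overweight ("Overweight prevalence Age 2–6 years").
- **One cell.** The term-birth row reads "37–40 weeks 92.3 4615 9230 1385".

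Elsewhere, the abstract expects more than 5000 newborns to be recruited, and Study design sets no upper limit on inclusions. Strengths and limitations repeats that the sample left after the 20% loss is large enough.

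**The concern.** A cohort with no upper limit on inclusions has one size commitment, its minimum. Here the minimum is attached to two different quantities: children with complete data to the end of the study, and children enrolled at the start. Under the article's own loss these differ by 1000 children. A team that stops at 5000 enrolled satisfies one sentence and misses the other, and a later reader cannot tell which figure to judge the study against.

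Table 1 has a related weakness. It supports the minimum size with expected case counts, but for outcomes that arise mainly after age 2 it uses the number enrolled, although the same section places the loss after two years. Eczema, wheezing and overweight are among the outcomes named in the Analysis plan, so a reader planning an analysis of them would take the printed counts as available cases.

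**Working it through.** **Inputs** (all from Study population size): enrolment scenarios of 5000, 10,000 and 15,000; loss of 20% after two years and about none before; prevalences of 7.5% (language disorders), 21.0% (eczema), 25.2% (wheezing), 16% (overweight) and 92.3% (37–40 weeks).

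**1. The plan's own figures**

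- Retained = enrolled × (1 − 0.20) = 5000 × 0.8 = 4000. This reproduces.
- Table 1 count = enrolment × prevalence. Counting the atopy range as two rows, the table holds 16 × 3 = 48 values, and 47 reproduce exactly with no attrition applied. The exception is in step 4.

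**2. Enrolment needed for the target as worded**

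Enrolled = complete / (1 − 0.20).

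- 5000 / 0.8 = 6250
- 10,000 / 0.8 = 12,500

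Enrolling 5000 therefore falls 5000 − 4000 = 1000 short of 5000 complete.

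**3. Later outcomes under loss**

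If a fraction d of children has been lost by the age of measurement, the printed count exceeds the available count by 1/(1 − d) − 1. The article bounds d between 0 (around age 2) and 0.20 (all loss already incurred):

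- d = 0: 1/1 − 1 = 0%
- d = 0.20: 1/0.8 − 1 = 25%

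Counts at the full 20% loss (0.8 × enrolment × prevalence), with the printed counts beside them:

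| Outcome | 5000 enrolled: printed / at 80% | 10,000: printed / at 80% | 15,000: printed / at 80% |
|---|---|---|---|
| Language disorders | 375 / 300 | 750 / 600 | 1125 / 900 |
| Eczema | 1050 / 840 | 2100 / 1680 | 3150 / 2520 |
| Wheezing | 1260 / 1008 | 2520 / 2016 | 3780 / 3024 |
| Overweight | 800 / 640 | 1600 / 1280 | 2400 / 1920 |

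The second figure in each pair is a lower bound. Where an outcome is measured before the loss has fully accrued, the available count lies between the two. Overweight recorded at the 24-month visit would be almost unaffected.

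**4. The gestational-age cell**

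- 15,000 × 0.923 = 13,845; printed 1385.
- The three printed cells in that column sum to 1035 + 1385 + 135 = 2555. With 13,845 they sum to 15,015, which agrees with 15,000 apart from rounding (the three prevalences add to 100.1%).
- The same row is right at 5000 (4615) and 10,000 (9230).

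**The case against.** The strongest defence is that Table 1 does what its labels say. Its caption and columns refer to enrolment scenarios, and the sentence right after it discloses the 20% loss and rests the adequacy claim on 4000 children. Children who withdraw after 12 months also still contribute data for the time they took part, with parental consent. This stands as far as it goes: the multiplication is correct and the loss is not hidden. It does not make the printed late-outcome counts available for analysis, and no loss-adjusted count is given beside them.

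A second defence is that nothing practical is lost. The intake has no maximum, so 6250 enrolments are not excluded, and even under full loss 300 to 1008 cases remain per late outcome at 5000 enrolled. That limits the severity, but it leaves the two statements of the target in conflict.

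Four stronger readings are tempting and are not supported:

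- **That the late-outcome counts are overstated by 25%.** This is only the upper end. The article gives no timing of loss after two years, so the range is 0% to 25%.
- **That the study is too small, or must enrol more.** The article declares 4000 sufficient, and nothing here shows an analysis becoming infeasible.
- **That the language row carries the wrong age because no routine visit falls at 3.5 years.** The label describes the cited national prevalence, not a study visit. Relabelling it would attach 7.5% to an age it was not reported for.
- **That the tenfold cell undermines the sizing.** It looks like a dropped digit, is too low rather than too high, sits in the largest scenario, and no other figure depends on it.

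**Conclusion.** The point holds, at minor to moderate severity. The core is the target: 5000 cannot be both the number with complete information over the study and the intake that leaves 4000. That conflict needs only the article's own 20% and does not depend on when the loss occurs.

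The Table 1 point is secondary. It rests on two assumptions: that the 20% loss applies to the children in whom these outcomes would be seen, and that its timing between ages 2 and 6 is unknown. The printed counts then lie 0% to 25% above the available ones. The 1385 cell is a plain misprint, to be corrected in passing.

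**What to change.** 1. State the target once, for one quantity. An example that needs no extra enrolment is: at least 5000 newborns enrolled, hopefully 10,000, with about 4000 (or 8000) expected to have follow-up to age 6. If the sponsor does mean 5000 complete, the matching enrolment of 6250 must be stated instead.
2. In Table 1, keep the enrolment-based counts. For the language, eczema, wheezing and overweight rows, add the counts at 80% retention (4000 / 8000 / 12,000 children), labelled as the lower bound if the full loss has occurred by the age of measurement.
3. Correct 1385 to 13,845.
4. Leave the 3.5-year label on the language row, since it belongs to the source prevalence.

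The cost is a short text and table correction. The late-outcome counts will look somewhat less favourable. Under the example wording, neither enrolment nor data collection changes.

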### Training and tutorial activities

Before the start of the study, family pediatricians will be involved in training activities. Local coordinators will be trained by the research team, and will be responsible for the training of their peers at the local level. A case report form (CRF) was created in an online form with the contribution of local representatives of family pediatricians and scientific committee participants. During an initial phase, a group of family pediatricians tested the electronic CRF (eCRF), leading to improvements and adding the necessary questions to achieve an eCRF that would allow a more complete and simple collection of data. The eCRF will be available online before the start of the enrollment period in order to let participating family pediatricians familiarize with the information that needs to be collected.

Central and local monitoring of the study will be scheduled with the aim to guarantee follow-up of the infants and the quality of data collected.

### Data collection

Data considered for the basic CRF are part of those routinely collected by the family pediatricians at the 7 standard well-child care visits scheduled for all children during their first 6 years of life, and data collected during each contact with the enrolled children. See Fig. 2 for the timeline of data collection, follow-up, and milestones in the NASCITA Study. In addition to the basic data, questions were added to allow the project to address specific areas such as nutrition, environment, and nurturing care. The eCRFs were consequently structured in a way that will permit us to expand data collection and analysis in these areas in a second phase. More specifically, in the future, distinct protocols will be created for potential sub-studies in these areas, also taking into consideration the research interests and expertise of the participating pediatricians in their design and in the identification of all useful data items. In order to enhance the quality of the data, the eCRF includes consistency and range checks to prevent internal inconsistencies, although the continuing review of collected data is guaranteed by the coordinating center and, in case of inconsistencies, pediatricians will be contacted. The administrators of the website (the coordinating center) will be able to view the completed forms also in a graphic format that will be updated periodically.

**Fig. 2 Fig2:**
[figure not shown]
Timeline of data collection, follow-up, and milestones in the NASCITA Study

### Baseline data

At the first visit (within 45 days of life of the newborn), parents will be asked about parental medical history, characteristics and lifestyle, indoor and outdoor environment, and circumstances during pregnancy and around birth. Pregnancy and perinatal data will be collected also through hospital discharge documents following delivery.

### Follow-up and outcomes

The primary outcomes of the study are measures of health of the newborns/children from birth until (at least) the age of 6 years. Health outcomes of children aged 0–6 years will cover different fields including: physical development, mental/cognitive development, nutrition and allergies, environmental exposures, and preventable infectious diseases. Table 2 provides an overview of data sources and collection at the different follow-up stages.

**Table 2 Tab2:** Overview of outcome measures collected by follow-up stage

Phase	Measurements
Baseline, T1 (within 45 days of life)	Demographic, socioeconomic, and health status of parents, details of pregnancy and perinatal routine, well-being of newborn, breast feeding/breast milk substitutes, living and social environment. Metabolic screening (notification). Anthropometric evaluation and physical examination. Immunization coverage. Infectious diseases. Dental health.
T2 (3 months of life)	Anthropometric evaluation and physical examination. Breast feeding/breast milk substitutes, child health, sleep. Hip ultrasound (notification). Vaccines (notification). Infectious diseases. Dental health.
T3 (6 months of life)	Anthropometric evaluation and physical examination. Neuromotor development assessment (Brazelton). Boel test. Breastfeeding status/Nutrition Vaccines (notification). Infectious diseases. Dental health.
T4 (1 year of life)	Child health, physical and psychological development, sleep, language development. Vaccines (notification). Breastfeeding status/Nutrition. Neurodevelopment evaluation. Infectious diseases. Dental health.
T5 (2 years of life)	Physical and cognitive development of child, child health, sleep, language development, and spoken language at home, media use. Language development. Breastfeeding status/Nutrition. Neurodevelopment evaluation. Vaccines (notification). Infectious diseases. Dental health.
T6 (3 years of life)	Anthropometric evaluation and physical examination. Child nutrition. Hearing check. Language development. Neurodevelopment evaluation. Vaccines (notification). Infectious diseases. Dental health.
T7 (4-6 years of life)	Physical and cognitive development of child, child health. Child nutrition. Neurodevelopment evaluation. Visual acuity examination. Vaccines (notification). Infectious diseases. Dental health.

### Analysis plan

The analysis plan for the NASCITA cohort entails the investigation of several exposures and outcomes in order to address numerous research questions.

The main independent variables that will be tested are:

Maternal/paternal age.

Education level.

Employment.

Marital status.

Parental health status.

Parental lifestyle habits (smoking, alcohol).

A few examples of the dependent variables are:

Vaccination in pregnancy.

Folic acid prophylaxis.

Birthweight.

Duration of breastfeeding.

Reading out loud.

Sleep position.

Overweight and obesity.

Neurocognitive development.

Prescription prevalence and appropriateness.

Nursery school attendance.

A few of these variables will be tested as both independent and dependent variables based on the kind of analyses (e.g., reading out loud will be the dependent variable while testing the influence of maternal age or educational level, but will be considered an independent variable when possible factors influencing children’s development are tested).

Examples of the NASCITA STUDY’S research questions are:

- the relationship between mothers’ age, education level, and geographic area (independent variables) and vaccination in pregnancy (Influenza and Tdap vaccines) (dependent variable);

- the association between maternal smoking in pregnancy (independent variable) and birthweight (dependent variable);

- the relationship between pregnancy, perinatal, and newborn growth characteristics and occurrence of adverse outcomes (i.e., obesity, hypertension, wheezing, eczema, hay fever, and asthma);

- the relationship between parents’ educational level (independent variable) and duration of breastfeeding (at discharge from hospital and at 3 and 6 months) (dependent variable);

- the relationship between parents’ educational level (independent variable) and children’s weight and BMI/percentage of overweight/obese status (dependent variable);

- the association between lifestyle factors and health inequalities and the trajectory of health in the preschool period;

- the association between geographical setting and nursery school attendance;

- the association between geographical setting and quality of care in terms of prevalence and appropriateness of drug prescriptions.

In all of the of the analyses, the effect of the geographic and environmental setting will be evaluated.

This type of general objective, involving numerous research questions, is similar to the goals of two Italian cohorts, the NINFEA [34] and the PiccoliPiù [16], as stated in their protocols.

Migrant newborns will be included in special subgroup analyses.

Categorical variables will be summarized using proportions and associations tested using chi-square or Fisher’s exact text, where applicable. Continuous variables will be summarized using means and standard deviations for normally distributed data, while skewed data will be summarized using medians. One-way ANOVA (F-value) will be used to test difference of means for normally distributed continuous variables and the *Mann Whitney U* test for skewed continuous variables. Statistical significance will be evaluated using a 95% confidence interval and a two-tailed *p-*value of < 0.05. Multivariate analyses will also be performed based on the study designs and outcomes to be evaluated.

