### Hypothesis and significance

We hypothesize that:

- differences due to environmental, sociodemographic, and parental determinants, as well as to child characteristics and physician attitudes, exist between geographic areas in a population’s health and in the use of health resources in the first few years of life;

- differences exist in the appropriateness of care provided by the National Health Service at different levels (regional, local, family pediatrician);

- differences exist between geographical settings in parental attitudes toward the recommendations concerning children’s health care and these differences may be a determinant of child development and well-being and health resource utilization;

- the existing differences between geographical settings in the opportunities for children to access educational/socialization experiences (e.g. day-care centers) may have an impact on development.

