**Fig. 1 Fig1:**
[figure not shown]
Geographical distribution of the NASCITA cohort

Italian healthcare is provided free or at a nominal charge through a network of Local Health Units (LHU). Each LHU consists of a number of healthcare districts, which are population-based territorial entities that aggregate different municipalities. Every Italian resident is registered with a family (pediatric or general) practitioner. Children are assigned to a pediatrician until they are 6 years old; afterwards, the parents can choose to register a child with a general practitioner. All adolescents > 13 years old are assigned to a general practitioner. In Italy there are about 7500 family pediatricians, for an average of 450.000 births/year [9]. About 60 newborns/year are therefore assigned to each pediatrician. All children are scheduled 7 well-child visits during their first 6 years of life (within 45 days of life and at 3, 6, 12, 24, 36, and 72 months of age). This list includes the recommended age for each well-child visit by the family pediatrician to ensure necessary preventive care, monitor a child’s growth and development, and establish a relationship between the child and his/her parents and the pediatrician.

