### Strengths and limitations of this study

NASCITA is entirely embedded in the child health care practice foreseen by the National Health Service and provided by family pediatricians. Recruitment and follow-up coincide with routine contact moments, so broad participation and follow-up rates are expected. Collaboration with other cohorts is foreseen. The NASCITA cohort data will be linkable and integrable with other data sources, such as routinely collected health data or data from other projects, as part of scientific collaborations.

High participation rates would allow an appropriate description and evaluation of all the different national territorial clusters. Moreover, NASCITA will provide opportunities to initiate new, experimental studies in subgroups of the cohort, and will contribute relevant information on determinants and health outcomes to policy and decision makers.

Since loss to follow-up is always a cause for concern in cohort studies and should be minimized, efforts have been made to establish a close and trust-based relationship with all participants. These efforts involve the creation of ad-hoc information material, the website, and newsletters to keep in touch with the study participants and to apply health promotion measures within the cohort. The estimated 20% loss to follow-up would, in any case, lead to a sample size that is large enough to be able to study common childhood exposures and outcomes. With the parents’ consent, data on children withdrawing after 12 months of age will be considered in the analysis.

A limit of the NASCITA study (as with any observational study) is the possibility of selection bias in the study population. The pediatricians recruited represent a co-operative sample, not a random sample, and should not be considered to be representative of the population of family pediatricians. The pediatricians, for example, could be more sensitive to better care practices or recommendations, and could influence the parents accordingly, promoting, for example, reading out loud to children. The target population of the study, however, will be the newborns (and their families) who are assigned to the pediatricians by the LHU based on places that have been freed up with those pediatricians. No selection bias in the population should therefore occur.

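### The named tests treat children as independent, so comparisons between areas and of practice-level characteristics would, as written, have p-values that are too small and intervals that are too narrow

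*Protocol article*

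**What the plan says.** The Analysis plan section fixes the tests. For categorical data it says: "Categorical variables will be summarized using proportions and associations tested using chi-square", or Fisher's exact test. Continuous data get one-way ANOVA or Mann-Whitney, and significance is judged at a two-tailed 5% level. The section adds that multivariate analyses will also be done, without naming a model.

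The same section makes geography part of every question: "In all of the of the analyses, the effect of the geographic and environmental setting will be evaluated". One of the study hypotheses is that "differences exist in the appropriateness of care provided by the National Health Service at different levels (regional, local, family pediatrician") and the other three also concern differences between areas or settings.

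Under Recruitment, volunteer pediatricians are enrolled first and then invite the families of their own newborns. Under Study area and setting, the practices lie in 22 geographic clusters, and practice size is described nationally: "About 60 newborns/year are therefore assigned to each pediatrician".

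On size, Study population size says that after 20% loss "the resulting sample size of 4000 children will still give NASCITA enough power to study common childhood exposures and outcomes". The Strengths and limitations section expects that "High participation rates would allow an appropriate description and evaluation of all the different national territorial clusters". Nowhere does the article mention within-practice correlation, a design effect, random effects or robust standard errors.

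**The concern.** Children in one practice share a doctor who prescribes for them, records their data and advises their parents. The Strengths and limitations section itself says that participating pediatricians may influence parental behaviour, and it gives reading aloud as an example. Reading aloud and prescribing are both listed as dependent variables. Some positive correlation within practices is therefore to be expected on the article's own account.

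A test that counts every child as an independent observation then understates the standard error of any contrast made between whole practices, which includes every contrast between areas. Ordinary variation among a few doctors can appear as a regional difference. Geographic and care-quality differences are central hypotheses, and the results are meant for policy makers, so false regional findings would matter.

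**Working it through.** **Inputs from the article**
- Minimum sample: "The aim is to recruit no less than 5000, and hopefully at least 10,000, newborns with complete information" (Study population size).
- Practice size: "In Italy there are about 7500 family pediatricians, for an average of 450.000 births/year" (Study area and setting).
- 22 clusters, 20% loss to follow-up, two-sided 5% level.

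**Input assumed**
- Intra-practice ICC. The article gives none, so 0.001 to 0.10 is shown.

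**The article's own figures**
- 450,000 / 7500 = 60 newborns per pediatrician per year: reproduced.
- 5000 × (1 − 0.20) = 4000 children: reproduced.
- No power figure, effect size or design effect is stated, so there is none to reproduce.

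**Implied structure (derived, not stated)**
- 5000 / 60 = 83.3 practices.
- 83.3 / 22 = 3.8 practices per cluster, if spread evenly.
- 5000 / 22 = 227 children per cluster.

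**Formulas for a contrast between groups of whole practices**
- Design effect: DEFF = 1 + (m − 1) × ICC, with m children per practice.
- Effective N = N / DEFF.
- Type I error, two groups of practices: 2 × [1 − Φ(1.96 / √DEFF)].
- Type I error, 22 areas: P(χ² on 21 df > its 95% point / DEFF).

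**Type I error of a nominal 5% test, m = 60, N = 5000**

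| ICC | DEFF | Effective N | Two groups | 22 areas |
|---|---|---|---|---|
| 0.001 | 1.06 | 4721 | 5.7% | 7.6% |
| 0.005 | 1.29 | 3861 | 8.5% | 24% |
| 0.01 | 1.59 | 3145 | 12% | 49% |
| 0.02 | 2.18 | 2294 | 18% | 82% |
| 0.05 | 3.95 | 1266 | 32% | 99% |
| 0.10 | 6.90 | 725 | 46% | about 100% |

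**After 20% loss, m = 48, N = 4000**
- ICC 0.01: DEFF = 1 + 47 × 0.01 = 1.47; 4000 / 1.47 = 2721.
- ICC 0.05: DEFF = 1 + 47 × 0.05 = 3.35; 4000 / 3.35 = 1194.
- ICC 0.10: DEFF = 1 + 47 × 0.10 = 5.70; 4000 / 5.70 = 702.

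**Simulation check.** One-way ANOVA was run on 83 practices of 60 children with no true area effect, 1000 runs per ICC. At ICC 0, 0.005, 0.01, 0.05 and 0.10 the 22-area test rejected in 4.8%, 26%, 47%, 99.7% and 99.9% of runs, in agreement with the formula. For a child-level exposure unrelated to practice, rejection stayed between 4.8% and 6.5%.

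**Precision.** The 16% outcome is the overweight prevalence in Table 1.
- One cluster: 4000 / 22 = 182 children. The 95% half-width is 1.96 × √(0.16 × 0.84 / 182) = 5.3 points. At ICC 0.05 it is 5.3 × √3.35, about 9.8 points.
- Two halves of the cohort at 80% power: (1.96 + 0.84) × √(2 × 0.16 × 0.84 / 2000) = 3.2 points. At ICC 0.05 it is 3.2 × √3.35 = 5.9 points.

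**The case against.** The strongest reply is that this is a condensed article, and that its multivariate analyses are left open. A multilevel or cluster-robust model is not excluded, and a fuller plan may contain one. This stands as far as it goes: a reader might infer that the final p-values will certainly be far too small, and the article does not support that. But the simple tests are named explicitly and are not limited to description, while no clustered method is promised.

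Other limits also stand:

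- **ICC.** The size of the effect rests on an assumed value. At 0.001 the inflation is slight.
- **Number of practices.** The figure of 83 comes from a national average and the minimum sample. With 10,000 newborns at 60 each there would be 10,000 / 60 = 167 practices. That improves precision but leaves the design effect, and so the type I error, unchanged.
- **Scope.** A reader might infer that the whole plan is affected. The listed main independent variables are parental characteristics, and child-level exposures unrelated to practice keep close to 5%.
- **Named practices.** Comparing particular practices with each other as fixed units does not incur this inflation. For the hypothesis about the family pediatrician, variation between practices is itself the object of study.
- **Power.** A reader might infer that the sample size calculation wrongly assumed independence. There is no such calculation. Table 1 gives expected case counts, and clustering does not change these. The statement about power is simply unqualified for area-level questions.
- **Contrasts.** The two-group and two-halves comparisons are illustrations; the article does not plan them.

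**Conclusion.** The point holds for comparisons between areas and of practice-level characteristics. For these, the named tests ignore a nesting that the article describes, and the error goes in one direction: p-values too small and intervals too narrow. With about 60 children per practice, the problem is slight at ICC 0.001. It becomes serious from about 0.005 for a test across 22 areas and from about 0.01 for two groups of practices. The sample of 4000 then carries less information on area questions than its count suggests, by a factor equal to the design effect (1.47 at ICC 0.01, 3.35 at 0.05). These sizes rest on the assumed ICC, equal practice sizes and the national average workload. The direction needs only a positive within-practice correlation.

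**What to change.** In the Analysis plan section, state that comparisons between areas and of practice-level characteristics, including the multivariate analyses, will use one of the following: a mixed model with a random intercept for pediatrician, GEE, or cluster-robust standard errors with the pediatrician as cluster. State that small-sample degrees of freedom will be based on the number of pediatricians. Keep the simple tests for description, or for child-level exposures unrelated to practice.

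In Study population size, and where Strengths and limitations repeats the claim, qualify the statement on power for area-level questions. Give detectable differences over a range of ICCs, for example 3.2 points without clustering and 5.9 points at ICC 0.05 for a 16% outcome in two halves of the cohort.

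The cost is wording, modest extra analysis work and less favourable stated precision. The analysis data set must keep a pediatrician identifier. The Data collection section implies that records can be traced to the pediatrician, since the center contacts pediatricians about inconsistencies, but it does not say so. Ethics and dissemination says that analyses use anonymized data, so retention of a coded identifier should be confirmed.
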